### Panel size and composition

2.6

As this study employs qualitative research techniques, a predetermined minimum sample size was not calculated. Participants in a Delphi study are expected to possess experience and expertise relevant to the subject under investigation. There is no consensus regarding the appropriate number of experts, and no standardized criteria for determining the sample size have been established (35).

A faster consensus can often be achieved when using smaller panel sizes. However, a smaller panel may mostly represent a more homogenous group, limiting the validity of extending the findings to a broader population. On the other hand, a larger panel size allows for greater heterogeneity among the participants, making the results more relevant for a broader range of individuals. With an increase in panel size, the reliability of findings also improves, reducing errors (36). However, the authors propose that Delphi studies with panel sizes exceeding 25–30 experts do not yield new ideas or significant enhancements in outcomes (36, 37). Sample size recommendations for the consensus group (38) range from 20 to 24 panelists per group, considered sufficient to fulfill the study’s objectives, and numerous studies have incorporated even fewer than 20 participants (39–41). As such, our initial selection will encompass at least 95 experts, factoring in an estimated dropout rate of 25% between subsequent rounds of questioning (36).

### Strategy to improve the response rate

2.7

The strategy to enhance the response rate will commence right from the outset of participant selection. The lead researcher ([name]) will contact each candidate to provide an overview of the study. Response rates will be boosted through a personalized approach, along with a clear explanation of the study process and an emphasis on the significance of their commitment to result validity (42).

After inclusion, participants will receive an email containing study details, supplemented by an email during the week preceding each round. The survey link will be emailed, and a text message will be sent to their mobile phones. To build rapport, regular email updates and social media announcements detailing study advancement will be disseminated throughout the process, including notifications about upcoming survey rounds.

Reminder emails will constitute a pivotal strategy to encourage the completion of each survey round, underlining the importance of their perspectives and stressing the necessity of completing the process for meaningful outcomes. When feasible, deadlines can be extended to accommodate participants’ schedules. Personalized reminder emails will be sent to establish a personal connection and motivate professionals to meet the deadlines. Participants will be informed about the number of completed rounds to foster a sense of achievement and inspire them to complete the round.

The lead researcher will facilitate communication with the panelists. Upon completing the survey, each participant will receive a personalized email expressing gratitude for their commitment to the project and survey completion.

### Data analysis

2.8

The sample will be characterized using descriptive statistics involving various measures such as count, mean, standard deviation, median, minimum, maximum, and range. Subsequently, each item’s count, mean, minimum, and maximum scores will be calculated and reported to participants following each study round. To assess the stability of responses, we will employ measurement of central tendencies with dispersion and analyze the percentage and frequency of distribution within the group. These strategies will help us evaluate the consistency and reliability of responses throughout the Delphi study rounds.

The statistical analysis will be conducted using the IBM Statistic Package for the Social Sciences software (IBM Corp. Released 2020. IBM SPSS Statistics for Windows, Version 27.0. Armonk, NY, USA: IBM Corp.).

For the analysis of free-text responses, an inductive thematic analysis procedure, as described by Braun and Clarke (43), will be performed independently by two team members. The QDA Miner Lite software will support this process. This method will facilitate the identification of emerging themes from data through stages encompassing pre-analysis, encoding, categorization, and data interpretation.

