	Identify individual barriers and resources for performing the exercise plan.
	Provide strategies for dealing with the identified barriers and coping in the future.

Critics have raised concerns about the limitations of traditional Delphi study designs in facilitating experts’ detailed explanations of their viewpoints (33). The present study will adopt a modified Delphi study design, as participants can elaborate on their opinions. In the initial round, they will also be prompted to identify any supplementary strategies they are familiar with or employ in their professional practice.

The survey will be developed using the Qualtrics platform (Qualtrics, Provo, UT, USA). Before it is applied, a pre-test will be conducted to assess comprehension and adequate functioning of the survey.

Each item will be evaluated using the Grading of Recommendations Assessment, Development, and Evaluation (GRADE) scale, which ranges from 1 to 9. The scale determines the significance of each item for inclusion: a score of 1–3 indicates it is not important for inclusion; 4–6 signifies importance, but not criticality; and 7–9 suggests it is critical for inclusion (34). The inclusion/exclusion criteria will consider items that achieve a ‘not important for inclusion’ or ‘critical-to-include’ rating in more than 75% of the responses. Given the absence of a clearly defined consensus criterion, we found this threshold and approach to be pragmatic and reasonable for consensus establishment, as they represents the perspective of three-quarters of the experts.

Items lacking consensus will progress to the subsequent round. Suppose there is no significant answer change about a specific item, characterized by a change of less than 20%. In that case, researchers will consider that consensus cannot be attained for that item and, therefore, exclude the item from subsequent rounds.

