**Figure 1 fig1:**
[figure not shown]
Flow chart to illustrate the stages of the Delphi process.

A total of 11 strategies have been identified for panel members to consider in Round 1 (Table 1). In Round 1, participants will access the online survey containing contextual details, survey instructions, and question-specific help resources. Demographic information will be collected, including age, sex, occupation, academic degree, years of work experience, and years of experience caring for patients with lower limb fractures. During this phase, participants will review the provided strategies and interventions, determining whether they wish to offer additional outcomes for consideration. Each survey item will feature a comment box where participants can suggest rephrasing, identify any omissions, propose new items, and offer reasons behind their choices.

The answers collected during each round will be aggregated and subjected to analysis. The summarized overview of data will be shared anonymously with participants as part of the introductory materials for the second round. This deliberate anonymity serves the dual purpose of fostering candid responses, as experts can contribute without being influenced by the input of their peers. Additionally, it empowers experts with the liberty to revise their initial responses if deemed suitable without any awareness on the part of their fellow experts. This confidentiality measure contributes to the integrity of the Delphi process and encourages genuine, uninfluenced participation.

In Round 2 participants will be asked to rate the appropriateness of the strategies as one that could be employed in patients with lower limb fractures. Following their ratings, participants will be asked to explain the reasons underlying their assessments.

In Round 3, the panel will have the chance to revisit their Round 2 responses for items where consensus is still pending. This opportunity arises from feedback on the group’s Round 2 responses. The overall process remains consistent with Round 2, albeit with a focus shift. Participants will be tasked with assessing the suitability of the interventions for potential implementation in patients with lower limb fractures. A fourth round will follow if consensus needs to be met after Round 3. During this round, panel members can reassess their Round 3 responses for items lacking consensus.

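### Panellists are shown count, mean, minimum and maximum per item, which for pending items do not show how close the panel is to the more-than-75% band rule

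*Protocol article*

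**What the plan says.** Section 2.4 (Data collection instrument) has every item rated on a "scale, which ranges from 1 to 9". Scores of 1–3 mean not important, and "4–6 signifies importance, but not criticality; and 7–9 suggests it is critical for inclusion". An item is settled, in or out, when the critical or the not-important band is the "rating in more than 75% of the responses". Items that do not meet this go to the next round. An item whose answers then change by less than 20% is treated as unable to reach consensus and is dropped.

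Section 2.5 (Rounds) makes group feedback the basis for reconsidering. On the chance to re-rate pending items in Round 3 it says: "This opportunity arises from feedback on the group’s Round 2 responses". On content it is general: "The summarized overview of data will be shared anonymously with participants as part of the introductory materials for the second round".

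Section 2.8 (Data analysis) is the only place that names the statistics fed back. For each item, the "count, mean, minimum, and maximum scores will be calculated and reported to participants following each study round". Percentages appear in the next sentence, but for the assessment of response stability, where the team will "analyze the percentage and frequency of distribution within the group". They are not said to go to panellists.

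**The concern.** The decision uses a band share, and the feedback list contains none. A mean on a 1–9 scale mixes how many panellists fall in a band with how far out the others lie. The minimum and maximum each depend on the single most extreme answer. A panellist asked to reconsider a pending item therefore cannot tell from these figures whether the panel is almost at the threshold with a dissenting minority, or is settled on important but not critical.

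Those situations call for different reflection, and re-rating after feedback is the step by which a Delphi panel moves to consensus or shows that it cannot. Under section 2.4 an item that hardly moves is excluded, so the information given at this step can bear on which items reach the care pathway.

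**Working it through.** The plan gives no figure to reproduce here. The check applies its own rule to possible sets of ratings.

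**Inputs**
- Scale 1–9, with bands 1–3, 4–6 and 7–9 (section 2.4).
- Consensus: strictly more than 75% of responses in 1–3 or in 7–9 (section 2.4).
- Feedback: count, mean, minimum, maximum (section 2.8).
- Panel size: section 2.6 says that "our initial selection will encompass at least 95 experts, factoring in an estimated dropout rate of 25% between subsequent rounds of questioning". Read as a 25% loss at each step, 95 becomes 95 × 0.75 = 71, then 95 × 0.75² = 53, then 95 × 0.75³ = 40. I use n = 40 for the worked pair.

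**Which items matter.** Only items without consensus are re-rated, so both items in the comparison must be pending. At n = 40, 75% is 30 responses, so consensus needs at least 31 in one outer band.

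**Two pending items with identical feedback (n = 40)**
- Item D: 11 ratings of 1, 28 of 7, 1 of 9. Sum = 11×1 + 28×7 + 1×9 = 11 + 196 + 9 = 216. Mean = 216/40 = 5.40.
- Item E: 1 rating of 1, 22 of 5, 16 of 6, 1 of 9. Sum = 1 + 110 + 96 + 9 = 216. Mean = 216/40 = 5.40.

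| | Count | Mean | Min | Max | % in 1–3 | % in 4–6 | % in 7–9 |
|---|---|---|---|---|---|---|---|
| D | 40 | 5.40 | 1 | 9 | 11/40 = 27.5 | 0 | 29/40 = 72.5 |
| E | 40 | 5.40 | 1 | 9 | 1/40 = 2.5 | 38/40 = 95.0 | 1/40 = 2.5 |

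The four planned statistics agree exactly. Item D is 31 − 29 = 2 votes short of inclusion; item E has almost no support for it. The three band percentages separate them at once. So does the median: the 20th and 21st ordered ratings are both 7 in D and both 5 in E.

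**A mean outside the majority's band.** With 70% of ratings at 7 and 30% at 1, the mean is 0.70×7 + 0.30×1 = 4.9 + 0.3 = 5.2. The item is pending (70% is not above 75%). Its mean lies in the important-but-not-critical band, where nobody voted, while 70% voted critical. This does not depend on n.

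**The case against.** The strongest reply has four parts.

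1. *The consensus decision is untouched.* The team applies the rule to the ratings themselves, so the feedback format cannot misclassify an item. This stands. A panellist who sees an item again can also infer that it has not reached consensus. That too stands, but it does not say how far from the threshold the item is, or in which band most ratings lie.

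2. *Mean and band share will usually agree.* When ratings cluster tightly, this is so. In some pending items the mean points where the majority is: 70% at 9 and 30% at 6 gives 0.70×9 + 0.30×6 = 8.1, well inside the critical band. The examples above need a split panel or a few extreme ratings. They establish possibility, not frequency.

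3. *The list may not be exhaustive.* Section 2.8 does not say that only these four statistics are sent, and section 2.5 promises a general summary. Count could also mean a frequency for each score, which would give the band shares. Beside mean, minimum and maximum, the natural reading is the number of responses, and nowhere does the article promise band percentages to panellists. If frequencies are intended, a clarifying phrase settles the matter.

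4. *Stronger readings are not supported.* A reader might infer that the minimum and maximum will suggest wide disagreement on nearly every item. That depends on how many panellists would give a 1, for which the article has no figure. If 2–5% would (assumed), the chance that the minimum is 1 is 1 − 0.98^71 = 76% to 1 − 0.95^71 = 97% with 71 respondents, and 66% to 93% with 53. At an assumed 0.5% it is 1 − 0.995^71 = 30% and 1 − 0.995^53 = 23%. The items come from a scoping review of motivational strategies, so very low ratings may be rare. A reader might also infer that the feedback misstates the group's position or steers panellists towards the mean. A correctly computed mean misstates nothing, and the article has no evidence on how panellists would react.

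**Conclusion.** The point holds as a mismatch between two stated methods: consensus is judged by band share, and the named per-item feedback contains no band share. For pending items the four statistics can be identical at 72.5% and 2.5% critical, and the mean can fall in a band that the majority did not choose. This rests on reading count as the number of responses and on the section 2.8 list being what panellists receive.

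The size is limited. How often such patterns will arise cannot be derived from the article, and the application of the consensus rule is unaffected. One might go on to conclude that items will be wrongly included or excluded, but nothing in the document shows this. What is shown is that panellists asked to reconsider may lack the figure by which their answers will be judged. That is worth correcting because it is nearly free and cannot be repaired once a re-rating round has been run on the less informative feedback.

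**What to change.** In section 2.8, add to the per-item feedback the percentage of ratings in 1–3, 4–6 and 7–9, or the full frequency distribution, preferably with the median and interquartile range. State that count means the number of responses to the item. The mean, minimum and maximum may stay. The stability analysis needs no change on this account, since it already covers central tendency with dispersion, percentages and frequencies.

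The change should be in the report template before the first feedback is sent. It needs no additional data and little extra analysis; the downside is a slightly longer feedback report.

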### Ethical considerations

2.9

The study will be conducted in accordance with the European Union General Data Protection Regulation and the Declaration of Helsinki (as revised in 2013). Therefore, the study protocol will be evaluated by an Ethical Review Committee. The initial page of the survey will feature a comprehensive elucidation of the study’s objectives and methodologies, accompanied by a guarantee that the researchers will ensure the confidentiality and anonymity of the data.

Participants must explicitly accept and agree to the online informed consent to proceed with the survey. The survey will have the options for participants to choose from “Yes” or “No,” indicating their understanding of the consent details and willingness to participate. Only those who affirmatively respond with a “Yes” to the informed consent query will be guided to the survey.

Participants who respond with “No” to the informed consent query will be guided to the survey’s conclusion, and their engagement will not be carried forward into subsequent rounds of the study. It will be entirely at the discretion of participants to determine whether to respond to any given question, modify their answers, or voluntarily quit at any time.

In strict adherence to ethical principles of anonymity and confidentiality, all data collected will be meticulously stripped of personally identifiable information, including any semblance of electronic identifiers.

All digital data will be coded, stored on a password-protected computer, and retained for 5 years. After this retention period, the lead researcher will destroy all data.

## Discussion

3

The present study protocol outlines a Delphi study to establish a motivational care pathway tailored for individuals with lower limb fractures based on expert opinions and consensus. We will use the Delphi method to systematically develop a comprehensive care pathway that guides the rehabilitation journey.

There is a need to innovate and introduce new tools to enhance patient experiences and health outcomes (32, 44, 45). This proposed care pathway is a prime example of such a tool, aiming to address the unique challenges of individuals with lower limb fractures. Its development can be a step forward in providing tailored solutions that can markedly improve the patient’s journey toward recovery and well-being.

The results of this research are expected to significantly impact clinical practice and are directly relevant. Creating a specialized care pathway will establish explicit standards expected to be adopted by health professionals. This standardization can revolutionize the approach to patient care, facilitating a more holistic and patient-centric approach. In essence, the resultant care pathway aims to streamline the rehabilitation process, enhance patient outcomes, and ultimately contribute to raising the standards for care provision within this domain.

Applying the Delphi method in this study guarantees the anonymization of all individual contributions, thus maintaining an equitable weighting of each expert’s input (36, 37, 42). The deliberate inclusion of experts from diverse professional backgrounds aims to comprehensively represent the multifaceted stakeholders involved in healthcare delivery. This strategic inclusion holds the potential to foster wider acceptance and integration of research findings.

The forthcoming results of this study have the potential to bridge existing gaps within the literature. By expert consensus, a dedicated care pathway to motivate individuals with lower limb fractures will be developed. Remarkably, this will be the first care pathway designed for this intention.

Notably, the current landscape lacks well-defined motivational guidelines or recommendations tailored to these patients, even though evidence underscores the distressing reality that fractures can trigger concerns about future mobility in older adults and engender the perception that the fracture signifies the end of independent living (16–18). This accentuates the need to create a care pathway that motivates these individuals to participate in rehabilitation programs.

Establishing clear, consensus-based recommendations could potentially yield advantages for these patients. These include an improved patient experience, heightened adherence to rehabilitation programs, and, ultimately, better health outcomes. The fruition of such recommendations could mark a pivotal advancement in patient care, addressing emotional and psychological factors alongside physical recovery.

This study is not without limitations. First, there’s the potential for expert selection bias, which can inadvertently occur if professional backgrounds are unevenly represented within the expert panel. This might impact the comprehensiveness and diversity of insights gathered during the study. To mitigate this potential bias, we intend to employ purposive sampling techniques. Second, there’s a risk of potential groupthink, a phenomenon where the iterative nature of the method could inadvertently induce experts to gravitate toward consensus. To counteract this, we will anonymizing participant data, to diminish this risk, fostering an environment where participants feel comfortable expressing their opinions without apprehensions tied to social dynamics or hierarchy. This approach will stimulate participants and open contributions. Finally, the Delphi method requires a significant investment of time due to its iterative process spanning multiple rounds of data collection. This prolonged process might strain participant commitment and hinder the feasibility of completing all intended rounds. To minimize this risk, we anticipated a dropout rate of 25% over the consecutive rounds of consensus development. In addition, we have designed a series of strategies to improve the response rate.

## Conclusion

4

This research protocol outlines a comprehensive approach to collecting expert opinions and achieving consensus through the Delphi method, to devise a motivational care pathway tailored for individuals with lower limb fractures. The findings can potentially fill gaps in the literature by guiding rehabilitation for individuals with evidence-based care pathways. The insights gathered with the development of this study have the potential to contribute significantly to improving patient care, offering tangible guidance for healthcare professionals to facilitate the recovery journey of individuals with lower limb fractures.
